## Abstract

**Background:**

In certain clinical situations, root canal treatment in teeth with apical periodontitis is performed in multiple visits, with the use of intracanal dressing between visits, aiming to reduce microorganisms and their by-products of the root canal system prior to filling. However, in recent years, discussions have been growing about the real need for the use of intracanal dressing in these cases. The use of ultrasonic activation of the auxiliary chemical substance has increased the potential for decontamination promoted during the chemomechanical preparation of the root canal. Thus, this study is designed to explore whether the use of intracanal dressing between visits during endodontic treatment favors periradicular repair in teeth with apical periodontitis.

**Methods:**

This is a randomized, prospective, double-blinded, controlled clinical trial designed to evaluate 3 distinct clinical approaches used during endodontic therapy: group 1—root canal treatment in a single visit (RCT-SV); group 2—root canal treatment in two visits with intracanal dressing (RCT-TVWD); and group 3—root canal treatment in two visits without intracanal dressing (RCT-TVWOD). A total of 150 adult patients aged 18 to 60, with at least one tooth diagnosed with asymptomatic apical periodontitis and periradicular lesion (confirmed with a cone beam computed tomography (CBCT)), will be randomized and will undergo one of the types of clinical approaches during endodontic therapy. Patients’ postoperative pain levels will also be recorded in periods of 24, 48, and 72 h and 7 days. Subsequently, clinical findings and long-term follow-up evaluations, with periradicular repair, will be performed at 6 and 12 months by intraoral periapical radiograph (IOPAR) and CBCT at the 24-month follow-up.

**Discussion:**

This study will evaluate the periradicular repair of mandibular molar teeth with apical periodontitis, providing information about the efficacy, benefits, and safety of performing the endodontic treatment in a single and two visits, with and without the use of calcium hydroxide dressing. All endodontic therapy procedures will be performed under a dental operating microscope and using ultrasonic activation of auxiliary chemical substances. These results may contribute to changes in the clinical approaches adopted during endodontic therapy of teeth with apical periodontitis and reveal the potential of complementary approaches that aim to enhance the decontamination of the root canal system during the preparation stage.

**Trial registration:**

ClinicalTrials.gov NCT05256667. Registered on 24 February 2022

## Administrative information

The protocol will be reported according to the Standard Protocol Items: Recommendations for Interventional Trials (SPIRIT) statement.

Note: the numbers in curly brackets in this protocol refer to SPIRIT checklist item numbers. The order of the items has been modified to group similar items (see http://www.equator-network.org/reporting-guidelines/spirit-2013-statement-defining-standard-protocol-items-for-clinical-trials/).

## Introduction

### Background and rationale {6a}

Endodontic therapy in teeth with apical periodontitis is premised on the elimination and inactivation of the greatest possible number of microorganisms within the root canal system through an efficient chemomechanical preparation and three-dimensional filling, allowing the repair of periapical tissues [1]. In cases of apical periodontitis, it is recommended that the efficient chemomechanical preparation should be able to promote cleaning, decontamination, and shaping, being aided by the use of intracanal dressing [2, 3]. Mechanical instrumentation plays a fundamental role in reducing the intracanal microbial load; however, around 30 to 40% of the walls of the main canal are not touched by the instruments [4], thus requiring the irrigating substance to perform an auxiliary chemical action during the instrumentation step [5]. 5.25% sodium hypochlorite (NaOCl) solution has shown satisfactory results due to its excellent properties, such as antimicrobial action, tissue dissolution, bleaching action, and debris removal [6]. Currently, the use of ultrasound as an irrigation intensifying agent associated with a 5.25% NaOCl solution on the root canal walls has been widely discussed [7, 8]. The transformation of electrical energy into mechanical energy using ultrasonic insertion inside the root canal causes a phenomenon in the irrigating solution called “cavitation,” which favors the cleaning and decontamination process of the root canal [9, 10]. Aiming to promote a complementary chemical action to the chemomechanical preparation of root canals, the association of calcium hydroxide [Ca(OH)2] with camphorated paramonochlorophenol (CMCP) and glycerin presents itself as an effective proposal for intracanal dressing to be used between clinical visits so that the dressing helps in the decontamination process, due to its resulting antimicrobial activity. In vitro studies have shown that the Ca(OH)2 paste containing CMCP has a broad antimicrobial spectrum eliminating microorganisms that are resistant to Ca(OH)2 and a wider range of antimicrobial action (eliminating microorganisms located in the most distant regions of the vicinity where the paste medicated was applied) and eliminates microorganisms more quickly than other pastes containing Ca(OH)2 associated only with inert vehicles such as water, saline solution, and glycerin [3, 11, 12].

In the current literature, there are several studies that compared endodontic treatments conducted in a single visit and in multiple visits in teeth with apical periodontitis or in similar conditions [1, 13–18], but the results found are divergent. There is a superiority of results for endodontic treatments conducted in multiple visits with the use of Ca(OH)2-based intracanal dressing in an animal model [13, 14] and in vitro studies [15]. In the most recent systematic reviews [16–18] and in randomized clinical trials [1, 19, 20], the results found are similar to each other in terms of success rate and postoperative pain. This divergence in results may be related to the use of different instrumentation techniques, irrigation, and intracanal dressing protocols in each of these studies, which makes a real comparison between them more difficult. Thus, the search for an efficient protocol for instrumentation and irrigation of root canals and a definition of the need for the use of Ca(OH)2-based intracanal dressing in the endodontic treatment of teeth with apical periodontitis is necessary.

### Objectives {7}

Our principal objective in this randomized, prospective, double-blinded, controlled clinical trial is to evaluate the effectiveness of endodontic treatments conducted in a single visit with the use of ultrasonic irrigant activation and in two visits with the use of ultrasonic irrigant activation and with and without the use of Ca(OH)2 dressing, in mandibular molars with asymptomatic apical periodontitis regarding periradicular repair during a period of 2 years of clinical, radiographic, and tomographic follow-up. Our secondary objectives are to analyze patients’ postoperative pain levels in periods of 24, 48, and 72 h and 7 days after the completion of a root canal; patient’s satisfaction rate with the treatment that will be performed; and patient’s preference regarding the frequency of clinical visit.

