### Intervention description {11a}

In order to treat apical periodontitis, in the first visit, the same endodontic instrumentation protocol will be performed for all teeth randomly divided into the 3 study groups. What will vary will be complementary and additional maneuvers such as the use of ultrasonic activation and intracanal dressing between visits of endodontic instrumentation. All endodontic therapy procedures will be performed under a dental microscope, except for anesthesia and rubber dam placement steps.

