##### Group 1—root canal treatment in a single visit (RCT-SV)

(1) The root canals will be filled in the first visit. In this group, a #30/.05 gutta-percha cone and epoxy resin-based sealer with the continuous heat wave technique and a final restoration with Z250 composite resin (3M ESPE, St. Paul, USA) will be used.

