#### Second clinical appointment

The second visit will include the following clinical protocol depending on the study group: for the 2 remaining groups (group 2 and group 3): (1) Anesthesia and restorative material removal. After local anesthesia with articaine hydrochloride and epinephrine tartrate injection (with 1:200,000 adrenaline [Produits Dentaires Pierre Rolland, Merignac, France]), all temporary restorative material from the tooth is removed. (2) Isolation and access. The tooth is isolated with a rubber dam and the root canal will be accessed one more time.

##### Group 2

(1) After 7 days, the intracanal dressing will be removed and the root canal will receive a new chemomechanical preparation, identical to the one performed in the first visit, and then it will be filled and permanently restored similarly to group 1.

##### Group 3

(1) After 7 days, the root canal will receive a new chemomechanical preparation, identical to the one performed in the first visit, and then it will be filled and permanently restored similarly to group 1.

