#### Secondary outcome measures

##### Patient’s postoperative pain using a questionnaire

Patients will answer a questionnaire for the analysis of postoperative pain, through the analog pain scale, in an interval of 24h, 48h, and 72h and 7 days: (0) no pain, (1) mild, (2) moderate, (3) severe, and (4) intense (Fig. 2).

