## Data collection and management

### Plans for assessment and collection of outcomes {18a}

Data associated with this study will be collected in the standardized case report forms (CRF) for the outcome analysis, and a specific supervisor will be responsible for reviewing the integrity, accuracy, and consistency of the data. To ensure the accuracy of data entry, three investigators (two endodontists and 1 radiologist) will be responsible for entering the data independently and data query forms (DQF) will be resolved by tracing the source data.

A questionnaire to score the patient postoperative pain levels will be administered by two investigators in periods of 24, 48, and 72 h and 7 days after the completion of a root canal treatment. Questionnaires of patient satisfaction rate with regard to the treatment and the patient preference in relation to the frequency of clinical visits will also be performed. The secondary outcomes will be obtained from self-administered questionnaires completed immediately after the completion of a root canal. All the data will be registered in document clouds (in a specific Microsoft 365 OneDrive institutional account files), and only authorized personnel will have access. Data monitoring will be independent from the investigators and competing interests.

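### Pain is timed from completion of the root canal, so group 1 is scored after a first preparation and the two-visit groups after a second, with no pain score scheduled between visits

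*Protocol article*

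**What the plan says.** Two sections fix the start of the pain clock. Objectives {7} sets the assessments at "24, 48, and 72 h and 7 days after the completion of a root canal", and Plans for assessment and collection of outcomes {18a} repeats it: "in periods of 24, 48, and 72 h and 7 days after the completion of a root canal treatment". The definition of the pain outcome gives the times without an origin: "through the analog pain scale, in an interval of 24h, 48h, and 72h and 7 days".

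On treatment, Intervention description {11a} states that "in the first visit, the same endodontic instrumentation protocol will be performed for all teeth randomly divided into the 3 study groups". For group 1, "The root canals will be filled in the first visit". Groups 2 and 3 wait 7 days, with and without a dressing respectively. Then, under Second clinical appointment, "the root canal will receive a new chemomechanical preparation, identical to the one performed in the first visit", and the tooth is filled and restored.

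Secondary outcome analysis compares pain between groups by the Kruskal-Wallis test. Section {18a} also says: "The secondary outcomes will be obtained from self-administered questionnaires completed immediately after the completion of a root canal".

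**The concern.** The same four time points mean different things in different groups. In group 1 they follow the first and only preparation of the infected canal. In groups 2 and 3 they follow a repeat preparation of a canal already prepared a week before, and the week after the first preparation has no scheduled score. The Discussion itself links postoperative pain to microbial pathogenicity and to debris pushed out during instrumentation, so the first preparation is a plausible source of pain.

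The Discussion also names fear of postoperative pain as a reason why single-visit treatment is questioned, and lists pain second among its four outcome parameters. A difference, or its absence, between group 1 and the two-visit groups would be read as a comparison of strategies, although only part of the two-visit strategy is scored.

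Separately, the two statements in {18a} cannot both apply to pain: a score at 24 h to 7 days is not completed immediately after treatment.

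**Working it through.** The plan states no figure for pain, so there is none to reproduce. The check sets procedures against the pain schedule, then illustrates size with assumed rates.

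**Step 1: coverage of the course**

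| | Group 1 | Groups 2 and 3 |
|---|---|---|
| Full preparations | 1 | 2, 7 days apart |
| Completion | Visit 1 | Visit 2 |
| Preparation that the pain week follows | First | Second |
| Preparations followed by scheduled scores | 1 of 1 | 1 of 2 |
| Days covered, to 7 days after completion | 7 of 7 | 7 of 14 |
| Scheduled readings | 4 | 4 |

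The allocation section gives 50 participants per group, so 2 × 50 = 100 patients have an unscored week.

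**Step 2: direction without assumed rates.** Unrecorded pain cannot be negative. Any summary of worst or ever-present pain over the whole course is therefore either right or too low in groups 2 and 3, and is complete in group 1.

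**Step 3: size under assumed rates.** Let p1 be the probability of pain in the week after a first preparation, taken as equal in all groups, and p2 the probability after a second. The article gives neither. Assume p1 = 20-50% and p2 = 25-100% of p1.

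- Observed difference, single minus two visits: p1 − p2.
- Whole-course two-visit risk if the two weeks are independent: 1 − (1 − p1)(1 − p2).
- Whole-course two-visit risk if second-week pain occurs only in patients who also had first-week pain: p1.

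| p1 | p2 | Observed difference | Two-visit whole course, independent | Whole-course difference, independent | Whole-course difference, nested |
|---|---|---|---|---|---|
| 20% | 20% | 0 | 1 − 0.80 × 0.80 = 36% | −16 | 0 |
| 20% | 5% | +15 | 1 − 0.80 × 0.95 = 24% | −4 | 0 |
| 30% | 15% | +15 | 1 − 0.70 × 0.85 = 40.5% | −10.5 | 0 |
| 50% | 50% | 0 | 1 − 0.50 × 0.50 = 75% | −25 | 0 |
| 50% | 12.5% | +37.5 | 1 − 0.50 × 0.875 = 56.25% | −6.25 | 0 |

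Differences are in percentage points; positive means more pain with single visit. Over the grid the observed difference runs from 0 to +37.5. The whole-course difference runs from −25 to −4 under independence and is 0 under full nesting.

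**Step 4: would it show?** For 30% against 15%, a two-sided 5% comparison of two proportions is significant with probability 0.57 at 70 teeth per group, or 0.43 at 50 patients per group. For 20% against 5% the figures are 0.77 and 0.62. With equal rates it is 0.05. The planned test is Kruskal-Wallis on an ordinal score, so these figures are only a guide.

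**The case against.** The strongest reply is that this is a declared endpoint: the objective is pain after completion, and the scores measure that. This stands for a claim limited to the filling visit. It does not make the contrast with group 1 like for like, since a first preparation is still compared with a second, and the article does not limit its conclusion in that way.

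Four stronger readings are tempting and are not supported.

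- *The observed comparison is biased against single visit.* This needs a second preparation to hurt less than a first. The article gives no such rate and describes the second preparation as identical, with the filling in the same counted week. At equal rates the observed difference is 0.
- *Flare-ups between visits are lost.* Adverse event reporting {22} lists flare-up and records symptoms, onset time and severity. What is missing is a score on the pain scale that enters the pain analysis.
- *The week is certainly never scored.* The contents of Table 1 could not be read. If it lists a score between visits, it conflicts with the time origin in {7} and {18a}, and the wording still needs correcting.
- *All pain comparisons fail.* Groups 2 and 3 share one time origin and a deliberately matched interval, so they can be compared for pain after completion. Pain while the dressing is in place, however, is not scored.

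The {18a} sentence on immediate completion may be loose wording meant for satisfaction and preference. It needs correcting but does not bear on the time origin.

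**Conclusion.** The concern holds for comparisons of group 1 with groups 2 and 3. As written, pain after a first preparation is compared with pain after a second, and 7 of 14 days have no scheduled pain score in the text for up to about 100 patients. That whole-course pain in the two-visit groups can only be understated needs no assumed rate.

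The size is not known. Under the assumed rates the plan would show 0 to 37.5 points against single visit, while the whole-course difference would be 0 to 25 points in its favour. The second range also assumes that pain after visit 1 is equally likely in all groups, although only group 1 is filled at that visit, and that the dependence between weeks lies between independence and full nesting. The point concerns a secondary outcome and leaves the primary outcome untouched. It should be fixed, because pain is one of the arguments on which the choice between one and two visits rests.

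**What to change.** 1. Give groups 2 and 3 the same questionnaire at 24, 48 and 72 h and 7 days after visit 1. The last reading falls on the day of visit 2.
2. Report pain by visit and over the whole course from the first preparation, for example as the worst score per patient. State that this takes a maximum over 8 readings in groups 2 and 3 and 4 in group 1. The extra week belongs to the two-visit strategy, but more readings also give more chances of a high score.
3. Keep patients already past visit 1 in the by-visit summary only. Recruitment began in August 2021, so their number may be substantial; the article does not give it.
4. If scores between visits can no longer be collected, limit the pain objective and conclusion to pain after the filling visit, and do not present it as a comparison of whole strategies.
5. Align the time origin in {7}, the pain outcome definition, {18a} and, if needed, Table 1. In {18a}, apply immediate completion to satisfaction and preference only.

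The cost is one more short questionnaire for up to about 100 patients and a few changes of wording. Treatment does not change.

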### Trial design {8}

This is a randomized, double-blinded, paralell group, non-inferiority controlled trial.

The trial protocol conforms with the Consolidated Standards of Reporting Trials (CONSORT) Statement. The trial design and protocol adhere to the Standard Protocol Items of the Recommendations for Interventional Trials (SPIRIT) criteria.

The study aims to compare the efficacy of endodontic treatments conducted in a single visit using ultrasonic irrigant activation and in two visits also using ultrasonic irrigant activation, with and without the use of calcium hydroxide dressing, in lower molar teeth with asymptomatic apical periodontitis (Fig. 1, “Study flowchart”).

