## Interventions

### Explanation for the choice of comparators {6b}

Traditionally, root canal treatment in teeth with apical periodontitis is performed in multiple visits, with the use of intracanal dressing between visits, aiming to reduce microorganisms and their by-products from the root canal system prior to filling. However, this type of conventional endodontic treatment has as a disadvantage the inconvenience of requiring patient return (in multiple sessions) for medication changes, until the root canal filling is possible. In the comparison group, the root canal treatment will be performed in a single session, which represents a more objective form of treatment, with the convenience of only one appointment for the patient and a lower operating cost for the professional.

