## Sample size and statistical methods

### Sample size details

The required sample size was calculated based on the preliminary outcome parameter of success, in a sequential approach, with each clinical case (tooth) serving as the statistical unit. Clinical studies that allow us to estimate, by means of CBCT, the repair index (complete absence of periapical radiolucency), therefore the success, after endodontic treatment of teeth with apical periodontitis and periradicular lesion, state that it is necessary to have a follow-up of at least 2 years to determine the success or failure of the treatment [22, 23]. After the first year of follow-up, post-endodontic treatment, it is still possible to observe the presence of periapical radiolucency in 52 to 84% of cases [1, 24, 25]. The sample will consist of 210 mandibular molars (first or second molars), based on statistical sample calculation, considering a power of 80%, an alpha value of 0.05, and an effect size of 20%. All patient characteristics at the beginning of treatment, such as age, gender, lesion size, among others, will be considered in the statistical analysis, in order to confirm the randomization of groups and the possible confounding effect of these characteristics.

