## Assignment of interventions: allocation

### Sequence generation {16a}

Assignments will be prepared by the statistician author of this study ([name]) prior to the trial start. A total of 150 patients (210 teeth) will be recruited and divided into 3 groups at a ratio of 1:1:1, namely, the RCT in a single visit, RCT in two visits with intracanal dressing, and RCT in two visits without intracanal dressing.

Randomization and allocation will be performed before all the clinical procedures.

First, a list of numbers from 1 to 210 will be created, each of the number represents one participant, then the list of numbers was assigned randomly following simple randomization procedures, by using Excel 2019 (Microsoft, Redmond, WA, USA) into three groups of 50 participants (70 teeth) each. Eventually, two columns in the spreadsheet are used, the first column contains the number of the participant (teeth) and the second contains the group to which the participant (teeth) is allocated, determined solely by the software.

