#### Main outcome analysis

The inter-group comparison of success rates will be analyzed using the Kruskal-Wallis test at 5% of the level of significance. For the missing data, the last observation carried forward (LOCF) method will be adopted to fill the validity analysis.

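### The trial is labelled non-inferiority, but its only primary analysis is an omnibus Kruskal-Wallis test, which uses no margin and cannot establish non-inferiority

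*Protocol article*

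**What the plan says.** Trial design {8} of the protocol article declares: "This is a randomized, double-blinded, paralell group, non-inferiority controlled trial". Main outcome analysis gives the only primary comparison: "The inter-group comparison of success rates will be analyzed using the Kruskal-Wallis test at 5% of the level of significance". The section on additional analyses {20b} plans none, and section {20c} adds only sensitivity analyses for missing data.

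Sample size details states the basis of the sample as "considering a power of 80%, an alpha value of 0.05, and an effect size of 20" per cent. It does not call the 20% a margin or a difference to detect, and gives no scale, sidedness or reference success rate. The result is: "The sample will consist of 210 mandibular molars (first or second molars), based on statistical sample calculation". Sequence generation {16a} divides this "into three groups of 50 participants (70 teeth) each".

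No section names a reference arm for a non-inferiority comparison. Explanation for the choice of comparators {6b} describes multiple visits with a dressing as the traditional treatment and adds: "In the comparison group, the root canal treatment will be performed in a single session". RCT-TVWD is therefore implied as the reference, but not named.

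**The concern.** The declared design and the fixed test have different null hypotheses. A non-inferiority null says that the new approach is worse by at least a margin, and the trial must reject it. The Kruskal-Wallis null says that the three arms do not differ. Rejecting it does not say which arm is worse, and failing to reject it says nothing about how much worse an arm could be.

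At stake is what the trial may conclude after 24 months of follow-up. Under a non-inferiority label, a non-significant result invites a conclusion that the test cannot bear, and the less precise the trial, the more likely that result becomes. This is not detail left to another document. The article itself fixes the test, and a margin stated elsewhere would have no role in it.

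**Working it through.** **Inputs from the protocol article.** 210 teeth, 70 per arm, from 150 patients (Sequence generation); alpha 0.05, power 80%, effect size 20% (Sample size details). No 24-month success rate is given. The nearest figure is at one year: "it is still possible to observe the presence of periapical radiolucency in 52 to 84% of cases", that is, 16-48% without radiolucency. Success rates below are therefore assumptions, shown as ranges, and teeth are treated as independent.

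**Step 1: the plan's own figure of 210.** It can be neither confirmed nor refuted.
- As an omnibus effect size of 0.20: chi-square with w = 0.20 and 2 df needs 241 teeth; analysis of variance with f = 0.20 needs 244. Power at 210 is 0.74 and 0.73.
- As a 20-point difference to detect: 75% v 55% at one-sided 0.05 gives 70 per arm, 210 in total; 80% v 60% at two-sided 0.05 gives 82 per arm, 246 in total.
- As a 20-point margin with equal arms, n = (z_alpha + z_power)² × 2p(1−p)/0.20². At p = 0.76, one-sided 0.025: 7.849 × 0.3648/0.04 = 71.6, so 72 per arm (216). At p = 0.65, one-sided 0.05: 71 per arm (213).

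Readings as a difference and as a margin both come near 210, each only at rates that the document does not state. The figure does not settle what the 20% means.

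**Step 2: what the test tests.** On a success/failure outcome, Kruskal-Wallis equals (N−1)/N times the Pearson chi-square with 2 df. It tests equality of three proportions. No margin appears in the statistic or in the critical value of 5.991.

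**Step 3: chance of a non-significant result when one arm is worse.** With arms (p, p, p−d) and mean p̄, the non-centrality is λ = 70 × Σ(pᵢ − p̄)²/[p̄(1−p̄)]. For p = 0.80 and d = 0.10: p̄ = 0.7667, Σ = 0.006667, λ = 70 × 0.006667/0.1789 = 2.61, and P(χ² < 5.991) = 0.72.

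| Other arms | 10 points worse | 15 points | 20 points |
|---|---|---|---|
| 60% | 0.78 | 0.56 | 0.31 |
| 70% | 0.77 | 0.53 | 0.28 |
| 80% | 0.72 | 0.45 | 0.20 |
| 90% | 0.58 | 0.27 | 0.08 |

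**Step 4: what a margin-based comparison could do with 70 per arm.** If two arms are equal at p, power to exclude a deficit M with a two-sided 95% interval is Φ(M/√(2p(1−p)/70) − 1.96). At p = 0.80 the standard error is 0.0676, so the half-width is 1.96 × 0.0676 = 13 points. For M = 0.10, Φ(1.479 − 1.96) = 0.32.

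| Success in both arms | 95% half-width | M = 10 | M = 15 | M = 20 |
|---|---|---|---|---|
| 50% | 17 points | 0.22 | 0.43 | 0.66 |
| 70% | 15 points | 0.25 | 0.49 | 0.73 |
| 80% | 13 points | 0.32 | 0.60 | 0.84 |
| 90% | 10 points | 0.51 | 0.84 | 0.98 |

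**Step 5: an illustration.** Suppose 49/70 succeed with a single visit and 56/70 in each two-visit arm. Kruskal-Wallis gives p = 0.27. The pairwise difference is −10 points with standard error √(0.7×0.3/70 + 0.8×0.2/70) = 0.0727, so the 95% interval runs from −24.2 to +4.2 points. The test is non-significant, yet the interval does not exclude even a 20-point deficit.

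**The case against.** The strongest reply is that the label is the error and the test is sound. The term non-inferiority describes the design once, while the objectives speak neutrally of evaluating or comparing effectiveness, and the Abstract asks whether a dressing favours repair, which is a question about a difference. A difference test suits that question and keeps its nominal 5% level. This stands, and is why removing the label is a full remedy.

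A reader might infer that the investigators will report a non-significant result as single visit being as good. No section states such a rule or makes such a claim. What the text supports is narrower: no result of this test could justify a non-inferiority conclusion.

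A reader might also infer that the trial was sized to detect a 20-point difference. The text says only "an effect size of 20" per cent, and the figure may have been meant as a margin. At a 20-point margin the trial is not hopeless: power is 0.84 at 80% success and 0.98 at 90%. Nor does the test miss most deficits of that size: the probability is 0.20 with the other arms at 80%.

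The primary measure is also described as the ordinal periapical index, for which Kruskal-Wallis is a natural choice. That does not help, because on an ordinal score it is still a difference test without a margin. Finally, a per-protocol set may properly be left to a fuller document, and its absence is not counted here.

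**Conclusion.** The contradiction is in the article's own text and holds whatever success rates are assumed: the declared design needs a margin-based comparison, and the one primary analysis is an omnibus test of equality.

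The practical size depends on assumptions. With 70 independent teeth per arm and the other arms at 60-80% success, a true deficit of 10, 15 or 20 points in one arm gives a non-significant result with probability 0.72-0.78, 0.45-0.56 or 0.20-0.31. With equal arms at 50-90% success, power to exclude those deficits is 0.22-0.51, 0.43-0.84 or 0.66-0.98. The 210 teeth come from 150 patients, so positive correlation within patients would make precision worse than these figures. By how much cannot be said, because the document gives no correlation.

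**What to change.** Make the label and the analysis agree, in one of two ways.

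(a) Delete non-inferiority from Trial design {8}, in line with the neutral objectives. Report pairwise differences in success with 95% confidence intervals, and state that a non-significant test will not be read as equivalence.

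(b) Keep the label. Name the reference arm (RCT-TVWD is the one implied). Fix and justify a margin before any 24-month outcome is seen by arm, and say whether the 20% is that margin. Base the conclusion on the two-sided 95% confidence interval for the difference in 24-month success, by a method that allows for several teeth per patient. Put the pairwise comparisons in a pre-set order. Restate the power that 70 teeth per arm gives for the chosen margin.

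Either way the cost is a protocol amendment with ethics approval in a trial that has been recruiting since August 2021. Option (a) gives up any formal non-inferiority claim. Option (b) may oblige the sponsor to publish a less favourable power: at 80% assumed success, 0.84 for a 20-point margin but 0.32 for a 10-point margin, before any allowance for clustering.
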